# Exploring acupuncture as a treatment for insomnia in perimenopausal women with stable angina pectoris: A protocol for a randomized, double-blind, placebo-controlled clinical trial

**DOI:** 10.1371/journal.pone.0301827

**Published:** 2024-04-18

## Abstract

**Background:**

Insomnia has emerged as a major public health issue jeopardizing human wellbeing. Furthermore, insomnia and angina arise concomitantly and exert reciprocal effects. Multiple studies suggest that perimenopausal females are more prone to experiencing both angina and insomnia, consequently substantially compromising their quality of life.Credible evidence suggests that acupuncture exerts a beneficial impact in alleviating insomnia. Nevertheless, the exhaustive investigation into the potential of acupuncture for mitigating insomnia co-occurring with stable angina in perimenopausal females remains a realm yet to be traversed in the realm of randomized controlled trials. Hence, the primary intent of this research protocol was to evaluate the effectiveness and safety profile of acupuncture when administered to perimenopausal subjects grappling with concomitant conditions of stable angina and insomnia.

**Methods:**

This study entails a single-center, randomized, double-blind, placebo-controlled clinical trial. A total of 110 patients exhibiting insomnia concomitant with stable angina in the perimenopausal period will be enlisted and randomized to either acupuncture or sham acupuncture. Participants in both arms will undergo 30-minute sessions thrice weekly over a 12-week intervention period, with a 12-week maximum follow-up. The primary outcome measure is the Pittsburgh Sleep Quality Index(PSQI). Secondary outcomes encompass the Health-Related Quality of Life Questionnaire (SF-36), Dosage of sleeping pills, SAP-associated evaluations, including C-reactive protein (CRP), lipoprotein-associated phospholipase A2 (Lp-PLA2), cardiac fatty acid-binding protein levels (C-FABP), and the Seattle Angina Questionnaire (SAQ). Additionally, the study includes assessments using the Hamilton Depression Inventory (HAMD) and the Generalized Anxiety Disorder Scale (GAD-7). Primary and secondary outcomes will be evaluated at baseline, 4 weeks, 8 weeks, 12 weeks (upon completion of the intervention), and at an additional 12-week follow-up. Any adverse events will be rigorously classified and characterized with respect to time of onset and abatement, therapeutic interventions implemented, impact on the primary morbidity, and regression.

**Discussion:**

The current study is poised to furnish pivotal clinical data on the utility of acupuncture for stable angina with concomitant insomnia in perimenopausal women, with the findings to be propagated through academic conferences and peer-reviewed publications.

**Clinical trial registration:**

Thai Clinical Trials Registry: TCTR20221121001. Registered 19 November 2022.

## Introduction

Stable angina pectoris (SAP), as a prevalent manifestation of coronary artery disease, exerts a pernicious impact on patients’ quality of life and portends a marked risk of progression to acute coronary syndromes [1–3]. In recent years, insomnia comorbid with SAP has garnered greater attention, with severe sleep disturbances emerging in numerous coronary artery disease patients [4, 5]. A preceding meta-analysis has demonstrated a robust correlation between insomnia and a heightened 45% susceptibility to cardiovascular disease morbidity and/or mortality in contrast to individuals exhibiting commendable sleep quality [6]. Given the precipitous decline in estrogen levels, perimenopausal women exhibit heightened vulnerability to coronary artery disease and insomnia [7].

The occurrence of angina pectoris may engender insomnia, which can adversely impact emotional regulation, cognition, memory, and systemic immunity, whilst also inflicting multi-organ damage including the cardiovascular system [8, 9]. In an 11-year longitudinal study, Sivertsen et al. identified insomnia as a salient risk factor for angina pectoris, cerebrovascular accident, and hypertension [10]. While sleep medicine research commenced in China in the 1980s, a formalized discipline remains nascent, and lay awareness of sleep hygiene remains negligible, with approximately 43% of Chinese citizens exhibiting varying degrees of sleep pathology, disproportionately afflicting women [11, 12]. The surging medical expenditures and diminished work productivity engendered by sleep disorders have emerged as pressing public health concerns [13].

Traditional physiotherapeutic modalities, behavioral therapeutic strategies, and psychotherapeutic interventions necessitate a manifold array of specialized personnel and material accoutrements, entailing an intricate interplay of multifarious determinants, encompassing even the specter of perilous remedial sequelae. Such comprehensive paradigms encounter formidable hurdles in their quest for pervasive adoption within clinical milieus. Pharmacological intervention, a modality ubiquitously resorted to, casts a prominent shadow within the therapeutic landscape. Among these, sedative agents emerge as the veritable cornerstone of clinical practice. Nonetheless, the protraction of drug administration over prolonged epochs exposes patients to the vicissitudes of drug reliance, counteractive resurgences, compulsive enthrallment, alongside a sundry constellation of untoward sequelae, underscored by the ominous propensity for withdrawal manifestations upon cessation [14]. In recent years, the clinical efficacy of acupuncture has garnered escalating recognition, with multiple studies elucidating its therapeutic utility for insomnia [15–17]. Acupuncture can enhance sleep quality by facilitating slow-wave sleep [18, 19], and it is also efficacious in the management of perimenopausal insomnia [20–23].

Recent investigations indicate a robust association between pneumonia induced by the 2019 novel coronavirus (2019-nCoV) and an elevated predisposition to angina and insomnia [24, 25]. While pertinent assessments of acupuncture’s efficacy in treating insomnia have been undertaken in the past, the onset of the 2019-nCoV pandemic has resulted in a significant paucity of current analyses of randomized controlled trials, especially concerning the specialized indication of concurrent angina and insomnia in perimenopausal women. In light of the paucity of data evaluating the efficacy and safety of acupuncture for insomnia specifically in perimenopausal patients with stable angina, we undertook this study.

## Materials and methods

### Trial strategy

A single-center randomized controlled trial has been designed to compare the effects of manual versus sham acupuncture in the management of insomnia comorbid with stable angina pectoris in perimenopausal women. The schedule for enrollment, interventions, and assessments is outlined in Fig 1, and the flowchart of the trial is shown in Fig 2. The SPIRIT (Standard Protocol Items: Recommendations for Interventional Trials) [26] checklist is delineated in the S1 Appendix.

**Fig 1 pone.0301827.g001:**
[figure not shown]
The SPIRIT schedule of enrollment, interventions, and assessment.

**Fig 2 pone.0301827.g002:**
[figure not shown]
Flowchart of the trial.

### Patients

This trial is slated to commence in March 2024, concluding in December 2024, with a target enrollment of 110 patients exhibiting insomnia comorbid with perimenopausal stable angina. Recruitment advertisements shall be situated in clinical environments, public venues, and online platforms to ensure adequate sample accretion. Eligible subjects shall be apprised of the prospective benefits and potential risks of participation, with written Participant Information and Consent Form (S2 Appendix) obtained to guarantee voluntary enrollment. Participants shall be considered successfully recruited upon provision of signed informed consent. All patients will receive conventional medications (e.g. aspirin, rosuvastatin, trimetazidine), plus lifestyle measures including dietary modification, appropriate exercise, and risk factor management.

### Diagnostic criteria

The diagnosis of stable angina pectoris followed the 2019 ESC Guidelines for the diagnosis and treatment of chronic coronary syndromes [27]. Coronary artery disease was established via coronary angiography, CT angiography or positive treadmill exercise testing. Patients exhibited Canadian Cardiovascular Society grade II-III angina, with a history of ≥30 days of stable angina, 2–5 anginal attacks per week.Insomnia was defined as Pittsburgh Sleep Quality Index >5 per the International

Classification of Sleep Disorders [28]. Questionnaires assessing insomnia duration and frequency were administered at admission by two blinded independent assessors, with consensus analysis to ensure consistent results. All enrolled patients exhibited self-reported insomnia of at least 30 days duration occurring ≥3 times per week.

### Inclusion criteria

Meet diagnostic criteria for both stable angina pectoris and insomnia as delineated above;Female gender, 45–55 years of age, in the perimenopausal period;No acupuncture treatment for minimum 6 months prior to enrollment;Provide informed consent and agree to randomized group allocation.

### Exclusion criteria

Not in perimenopausal phase;Severe renal, hepatic, hematologic or other systemic diseases;Psychiatric disorders or impaired consciousness;Uncontrolled severe hypertension, diabetes mellitus or malignant arrhythmia;valvular disease, Recent acute myocardial infarction, unstable angina, myocarditis, hypertrophic cardiomyopathy, or post-pacemaker severe heart failure (NYHA grade ≥III);Major surgery, trauma, bleeding event or severe infection within past 3 months;Insomnia attributable to medications, alcohol or environmental factors;Local skin infections near acupoint sites;Malignancy or hyperthyroidism;History of syncope or severe needle phobia;Any other condition potentially interfering with study participation or completion as deemed by the investigator.

### Criteria for withdrawal and termination

Per ethical imperatives safeguarding patient autonomy, subjects retain the prerogative to withdraw from the study at any juncture for any reason. For subjects electing withdrawal, the rationale must be meticulously documented and incorporated as an evaluative metric for trial cessation. Clinical investigators should fastidiously document the basis for trial termination and its pertinence to the study, with analysis of the potential impact of the endpoint event on study conclusions.

All primary data on study withdrawals and terminations will remain sealed for examination upon trial completion. Moreover, grounds for termination include: any adverse events arising during the study; comorbidities, complications, or physiological alterations precluding ongoing participation; poor treatment compliance; contraindicated interventions; missed visits; and unblinding events.

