### Blinding

The allocation of groups will remain concealed from patients, evaluators, and data analysts. The acupuncture points and techniques will be comparable between the two groups. The control group will undergo sham acupuncture with a non-penetrating device mimicking the look of real needles to preserve blinding [29], see Fig 3. To evaluate the success of blinding, we will survey participants on their belief about receiving either genuine or sham acupuncture after the intervention. Due to the distinct nature of performing acupuncture, blinding the practitioners is not feasible.

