### Treatment group

Sterile acupuncture needles of 0.30 mm diameter and 40 mm length were utilized (Hualun Medical Appliance Co, Ltd, Suzhou). The acupuncture points were identified and localized conforming to the World Health Organization’s standards. The prescribed acupoints were PC6 (Neiguan), EX-HN3 (Yintang), KI6 (Zhaohai), RN17 (Danzhong), HT3 (Shaohai), and SP6 (Sanyinjiao). EX-HN3, and RN17 were inserted to a depth of 5-10mm, while KI6, PC6, HT3, and SP6 were inserted perpendicularly until reaching 20-25mm depth. The acupuncture procedure consisted of: disinfecting the skin and instruments; needle insertion at the acupoints, rotating bidirectionally between 90°-180° at 60–90 rotations/min until Deqi sensations of numbness, fullness, soreness, and aching were elicited, quantified using the Chinese Modified Massachusetts General Hospital Acupuncture Sensory Scale (C-MASS). Each 30-minute acupuncture session incorporated manual stimulation for 1 minute every 10 minutes.

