### Control group

After performing the same sterilization procedures as the treatment group, the sham acupuncture group utilized blunt-ended needles (Hualun Medical Appliance Co, Ltd, Suzhou) of 0.30 mm diameter and 40 mm length to administer non-penetrative needling at non-acupoints (selected stimulation points close to the treatment group’s acupoints but outside the meridians and avoiding the distribution of the body’s nerves). Specific non-acupoints selection are shown in S1 Table. The treatment duration matched that of the treatment group, however the blunt needles (Fig 3) were only tapped lightly on the skin surface without tissue penetration or manipulation to elicit Deqi. Sham-needle stimulation was simulated for 1 minute at 10-minute intervals during the 30-minute treatment.

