### Primary outcomes

The Pittsburgh Sleep Quality Index (PSQI), comprising 19 self-rated and 5 hetero-rated items, will be employed to evaluate the primary outcome of global sleep quality over the past month across 7 components: sleep duration, sleep latency, sleep efficiency, sleep medication use, sleep disturbances, subjective sleep quality, and daytime dysfunction. PSQI will be assessed at baseline, after each 4-week treatment phase (weeks 4, 8, 12), and during follow-up at weeks 16 and 24.

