### Patients’ safety and adverse events

Safety assessments were conducted at each study visit including: vital signs (temperature, blood pressure, respiration rate, heart rate); routine blood and urine tests; liver and renal function tests; electrocardiography. All adverse events were monitored, managed, and reported according to standard operating procedures detailing time of onset, duration, severity, interventions, and outcome. Adverse events will be collected according to the standardized methodology Common Terminology Criteria for Adverse Events (CTCAE). Trial suspension or withdrawal would be determined by the investigator contingent on adverse event severity. Any serious adverse event must be reported to the principal investigator and ethics committee within 24 hours.

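### The termination grounds have no severity threshold and do not separate stopping needling from leaving the study; if used to end participation, they undercut the intention-to-treat analysis

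*Protocol article*

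**What the plan says.** The section Criteria for withdrawal and termination first protects a woman's right to leave at any time. It then says that "grounds for termination include: any adverse events arising during the study; comorbidities, complications, or physiological alterations precluding ongoing participation; poor treatment compliance"; the list ends with "poor treatment compliance; contraindicated interventions; missed visits; and unblinding events". It also asks investigators to document the basis for termination, "with analysis of the potential impact of the endpoint event on study conclusions".

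Four other sections bear on this:

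- **Patients' safety and adverse events:** "Trial suspension or withdrawal would be determined by the investigator contingent on adverse event severity".
- **Primary outcomes:** "PSQI will be assessed at baseline, after each 4-week treatment phase (weeks 4, 8, 12), and during follow-up at weeks 16 and 24".
- **Statistical analysis:** all randomised women enter the intention-to-treat analysis, whether or not they complete the study.
- **Blinding:** "we will survey participants on their belief about receiving either genuine or sham acupuncture after the intervention". No removal is attached to the answer.

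**The concern.** Every ground on the list arises after randomisation. Two features of the wording cause trouble.

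First, the adverse-event ground has no threshold. A small bruise meets it as literally stated, while the safety section calls for a judgement of severity. Two members of staff could each follow the text and act differently.

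Second, the list does not separate stopping treatment from leaving the study. The section heading, the ground about events that preclude further participation, and the inclusion of missed visits all lean towards leaving. If the list is applied that way, later PSQI scores are not collected. The women who still have a week-12 score may then no longer be comparable between arms, and membership of the intention-to-treat set does not repair that. Bias is the main worry, and loss of power comes second.

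**Working it through.** **1. The adverse-event wording.** The termination section admits any adverse event. The safety section makes withdrawal contingent on severity and leaves the decision to the investigator. Neither refers to the other. They can be reconciled (an event may be a ground, and severity decides whether it is used), but the reader has to supply that link. The two are not aligned, though they do not flatly contradict each other.

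**2. Which grounds could differ by arm.**

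- *Adverse events: plausible.* In the acupuncture arm "KI6, PC6, HT3, and SP6 were inserted perpendicularly until reaching 20-25mm depth", the other two points are needled to 5-10 mm, and needles are rotated until Deqi. Sham needles are "only tapped lightly on the skin surface without tissue penetration or manipulation to elicit Deqi".
- *Unblinding: only if a woman recognising her allocation counts as an event.* The article does not say that it does.
- *Missed visits and poor compliance:* the article gives no arm-specific mechanism, though both could relate to how a woman is responding.

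**3. The plan's own sample size (Sample size section).** Inputs: δ = 11.43 − 9.20 = 2.23, SD 3.24, α = 0.05 (taken as two-sided), power 90%.

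n = 2 × [(1.960 + 1.282) × 3.24 / 2.23]² = 44.36 per group. The article states 44. Then 44 / 0.8 = 55 per arm, or 110 in total, which agrees.

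**4. Illustration of loss from the missed-visit ground.** The article gives no rate of missed visits, adverse events or unblinding, so the rates here are assumptions. Strict reading: missing the week-4 or week-8 visit ends follow-up. Misses are taken as independent with probability p per visit. Women who miss week 12 itself are left out, because they lack the score in any case.

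Extra week-12 loss = (1 − p) − (1 − p)³. Numbers per arm with a week-12 score are 55(1 − p) without the ground and 55(1 − p)³ with it, rounded down. Power is for a two-sample t-test, two-sided 0.05, δ = 2.23. The second SD is √((2.11² + 3.24²)/2) = 2.73, from the two SDs in the article.

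| p | Extra loss | Of 110 | Per arm, without / with | Power, SD 3.24 | Power, SD 2.73 |
|---|---|---|---|---|---|
| 2% | 3.9% | 4.3 | 53 / 51 | 93.9% / 93.1% | 98.6% / 98.3% |
| 5% | 9.3% | 10.2 | 52 / 47 | 93.5% / 91.0% | 98.5% / 97.5% |
| 10% | 17.1% | 18.8 | 49 / 40 | 92.1% / 86.0% | 97.9% / 95.0% |

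If the same women miss repeatedly, the extra loss is smaller. On these assumptions the power cost is small to moderate.

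**5. Bias, as an identity only.** Retained mean − full-arm mean = f × (retained mean − removed mean), where f is the fraction removed. With f = 0.10 and a hypothetical difference of 1 to 3 PSQI points, that arm's mean shifts by 0.1 to 0.3 points. Nothing in the article fixes f, the difference or its sign.

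**The case against.** The strongest reply is that the list is permissive. It says what the grounds include, it does not order removal, and the safety section supplies the discretion. *Termination* is also ambiguous: the same section speaks of ending the trial, and some grounds concern treatment. The PSQI schedule runs to week 24 without exception, and the analysis section excludes no randomised woman. Finally, this is a journal article, and follow-up after stopping treatment is commonly set out in the full protocol.

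Much of this stands. A reader might infer that any adverse event or missed visit must end a woman's follow-up, that the two sections flatly contradict each other, or that the intention-to-treat analysis is already broken. The article supports none of these: it nowhere says that outcome collection stops, and it gives no rates from which a loss could be derived.

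The reply does not remove the stated list. Compliance and missed visits are events in individual women, so the list is not only about closing the trial. A missed visit fits poorly as a reason to stop needling alone. The general PSQI schedule does not say that it overrides termination. The impact analysis that the section asks for cannot recover scores that were never collected. What remains is a rule the article itself states, and states loosely, so this is more than absent detail.

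**Conclusion.** The point holds in a conditional form and is minor. The termination grounds carry no severity threshold, are not aligned with the safety section, and do not separate stopping needling from leaving the study. If they are used to end participation, PSQI scores will be missing after post-randomisation events, some plausibly arm-related, and the intention-to-treat comparison is weakened.

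Neither the size nor the direction of any bias can be derived from the article, and a breach of the 20% allowance for loss cannot be shown. The loss and power figures are illustrations that rest wholly on assumed rates, independent misses and a strict reading of one ground. Even so, power stays at 91% or more in five of the six cases, with a lowest value of 86%.

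**What to change.** Amend the section on withdrawal and termination to state that:

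- the listed grounds may stop study needling only;
- the adverse-event ground follows the investigator's severity decision in the safety section;
- missed visits and poor compliance are not reasons to end participation;
- unblinding is recorded, and the woman is not removed;
- PSQI and the other scheduled assessments continue to week 24 unless she withdraws consent to follow-up, and she is analysed in her randomised arm.

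This is a cheap improvement. It costs a short amendment and some extra questionnaire follow-up (by phone if needed) of women who stopped treatment. It needs no additional patients or procedures, and the right to withdraw is unchanged. The Trial status section says that recruitment has begun, so it is best done soon: scores not collected on time cannot be obtained later.

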### Sample size

The Pittsburgh Sleep Quality Index (PSQI) score following the full acupuncture intervention regimen was utilized to determine the requisite sample size. Statistical significance was defined as α = 0.05 with a power of 90%. Based on a prior study, perimenopausal women with insomnia had mean±SD PSQI scores of 11.43±2.11 with sham acupuncture and 9.20±3.24 with manual acupuncture [30]. Using the sample size formula:

$$n=2\times {\left[\;\frac{\left(Z_{\alpha }+Z_{\beta }\right)\times \sigma }{\delta }\;\right]}^{2}$$

Using the larger standard deviation of 3.24, with δ = 11.43–9.20 = 2.23, β = 0.1, 1-β = 0.9, and α = 0.05. The resultant sample size required per group was 44. Allowing for a 20% loss to follow-up, the total sample size needed for the study was 110 participants.

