### Statistical analysis

Group allocation will be concealed from the statistician. All randomized participants will be included in the intention-to-treat (ITT) analysis, regardless of study completion status. To ensure accuracy, double data entry will be performed. Statistical analyses will be conducted using SPSS 24.0. Continuous variables will be summarized as mean ± standard deviation or median (interquartile range). Between-group comparisons will utilize two-sample t-tests or Wilcoxon signed-rank tests for skewed data. Within-group baseline to endpoint changes will be analyzed by repeated measure analysis of variance (ANOVA), with a primary focus on assessing interactions between groups and time. Categorical variables will be compared using Fisher’s exact or Chi-square tests. Statistical significance will be defined as p<0.05.

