## Limitation

This study has several limitations. A major challenge in acupuncture trials is the inability to blind the acupuncturist, while elicitation of Deqi sensation is integral to efficacy, confounding participant blinding with current methods. Second, subtle variations in needling technique and localization are inherent between acupuncturists and individuals. Thus, extensive standardized pretrial training is imperative to minimize practitioner variability.

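### Terminating participants for unblinding events, with blinding checked only after the intervention, can flatter the blinding check and cost PSQI data

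*Protocol article*

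**What the plan says.** All references are to the protocol article.

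- **Criteria for withdrawal and termination.** The list of grounds ends with "poor treatment compliance; contraindicated interventions; missed visits; and unblinding events". An unblinding event is not defined. The same section asks investigators to document the basis for each termination and to analyse its possible effect on the conclusions.
- **Blinding.** "The allocation of groups will remain concealed from patients, evaluators, and data analysts". Of the practitioners it says that "blinding the practitioners is not feasible". The one check described is that "we will survey participants on their belief about receiving either genuine or sham acupuncture after the intervention".
- **Control group.** The sham needles are "only tapped lightly on the skin surface without tissue penetration or manipulation to elicit Deqi". Under Treatment group, real needles penetrate and are rotated until Deqi is felt.
- **Limitation.** The article concedes that "elicitation of Deqi sensation is integral to efficacy, confounding participant blinding with current methods".
- **Statistical analysis.** "All randomized participants will be included in the intention-to-treat (ITT) analysis, regardless of study completion status".
- **Primary outcomes.** The PSQI has 19 self-rated and 5 other-rated items. It is taken at baseline and at weeks 4, 8, 12, 16 and 24.

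**The concern.** The blinding survey is the article's only stated evidence that participants stayed blind, and the primary outcome is mainly self-rated. A check of this kind has to include the women most likely to have been unblinded. Under the stated rule, a woman known to be unblinded may be terminated before the survey takes place. The survey would then be conditioned on the very thing it is meant to detect, and the error runs one way, towards reassurance.

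The outcome data are also at stake. Termination for an unblinding event depends on something learned after randomisation and tied to the treatment received. If it ends follow-up, the later PSQI scores are missing for that reason. Because patients, evaluators and analysts are all meant to be blind, the term could also cover a staff error. A woman might then be lost although her own ratings were unaffected.

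**Working it through.** **1. Does the rule act on individual women?** Its neighbours in the list are poor compliance, missed visits and conditions that prevent a person from continuing. These apply to a participant, not to the trial as a whole, so unblinding events are most naturally read the same way.

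**2. Order of events.** Unblinding can occur at any time in the 12-week course, and the survey comes after the intervention. Nothing says that terminated women are surveyed, and nothing says that they are not.

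**3. The plan's own figures.** The Sample size section gives δ = 2.23, SD = 3.24, α = 0.05 and 90% power. Two-sided, n = 2 × [(1.960 + 1.282) × 3.24 / 2.23]² = 44.36, which the article gives as 44 per group. With 20% loss, 44 / 0.8 = 55 per arm, or 110 in total. The stated size reproduces and is not in question.

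**4. Effect on the survey.** The article gives no unblinding rate, so every rate here is an assumption. Let s be the share of an arm who are sure of their allocation, and r the share of the arm who are sure and are removed unsurveyed. The survey then shows (s − r) / (1 − r).

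| Truly sure (s) | Part of these removed | r | Survey shows |
|---|---|---|---|
| 30% | none | 0 | 30% |
| 30% | one woman of 55 | 0.018 | 0.282 / 0.982 = 28.7% |
| 30% | a quarter | 0.075 | 0.225 / 0.925 = 24.3% |
| 30% | half | 0.15 | 0.15 / 0.85 = 17.6% |
| 30% | three quarters | 0.225 | 0.075 / 0.775 = 9.7% |
| 20% | half | 0.10 | 0.10 / 0.90 = 11.1% |
| 40% | half | 0.20 | 0.20 / 0.80 = 25.0% |

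The first two rows correspond to a narrow meaning of the term (a rare code break), and the others to a broad one.

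A second illustration points the same way. Suppose a share u of an arm learn their allocation and all are removed, while the rest guess at 50/50. The true correct-guess rate is u + (1 − u)/2, which is 52.5%, 55%, 60% or 65% for u = 5%, 10%, 20% or 30%. The survey of those who stay shows 50% in every case.

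**5. Effect on numbers and power.** Removals are taken on top of the planned 20% loss, with power = Φ(δ / [SD × √(1/n₁ + 1/n₂)] − 1.96).

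| Removed, sham / active | n sham, n active | Power |
|---|---|---|
| 0% / 0% | 44.0, 44.0 | 89.8% |
| 5% / 5% | 41.8, 41.8 | 88.2% |
| 20% / 5% | 35.2, 41.8 | 85.3% |

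Even the unequal case costs only a few points of power. The main issue is who is missing, not how many.

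**The case against.** The strongest reply is that the harm depends on two things the article does not say.

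First, an unblinding event may mean only a code break or a disclosure by staff. The Blinding section treats a woman's belief as a separate matter, to be measured by survey, and no procedure is described for asking about or logging beliefs during treatment. A reader might infer that every woman who works out her arm leaves the trial, but the text does not support that. On the narrow meaning few women are affected. This stands, and it limits the expected size.

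Second, termination may stop treatment without stopping the survey or the visits, and the full protocol may say so. This also stands as a possibility. However, the article states the rule without that reservation, and its wording points towards the end of participation.

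Two further inferences go too far:

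- **That the arms will be depleted unequally.** Light tapping without Deqi may reveal the sham, but penetration and Deqi may equally reveal real needling. The Limitation section gives no direction, and equal discovery would leave the arms balanced.
- **That the rule contradicts the intention-to-treat statement.** That statement foresees women who do not complete and keeps them in the analysis. It cannot supply scores that were never collected, so it is undermined rather than contradicted. It also governs the outcome analysis, not the survey.

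The requirement to document each termination and consider its effect is useful. It creates a record, but recovers neither the woman's belief nor her later PSQI scores.

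**Conclusion.** The point holds in conditional form. If women terminated for unblinding are not surveyed or followed, as the text implies without stating, the blinding check is selected towards apparent success. PSQI data are then lost for a post-randomisation reason that may differ by arm, which weakens the intention-to-treat analysis.

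The size cannot be fixed from the article. On assumed rates, 30% truly sure would appear as anything from nearly 30% (one removal) to about 10% (three quarters of them removed), and as about 18% if half are removed. These figures assume that every removed woman was sure of her arm and that all who remain answer.

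A reader might also conclude that such removals would use up most of the loss allowance. Removing 15% of one arm of 55 is 8.25 women. That is three quarters of that arm's allowance of 11, but only 8.25 / 22 = 37.5% of the trial's, and the 15% is itself assumed. No sample-size figure needs to change.

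**What to change.** Add to Criteria for withdrawal and termination that an unblinding event does not end outcome assessment, whatever is decided about treatment. The rule for stopping treatment is left alone. Then:

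- define an unblinding event, and say whether a woman's own discovery counts;
- log the date, who was unblinded (participant, evaluator or analyst) and how;
- take the belief survey from the woman at that time;
- continue all scheduled PSQI assessments and analyse her in her randomised arm;
- report the events by arm beside the survey result, with these women in its denominator.

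The cost is one log entry and one brief survey per event, with no extra patients. If the full protocol already provides for this, a sentence in the article is enough. Trial status reports that recruitment is under way, so the change should come soon: a belief not recorded when it arises cannot be recovered later.
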